### 2.10. Procedure

All 1st- and 2nd-year students of Physical Education will be informed of the research procedures, and those that are interested will be provided with a brief introduction to the selection process. One researcher from the university will conduct a pre-screening self-administered questionnaire (on paper) during classes with students. The pre-screening will address basic demographic data, the frequency of LBP, and the specific inclusion and exclusion criteria for this study. LBP will be assessed using the following question: “Have you experienced low back pain for the last 3 months?”. The answer options were: “no”, and “yes”. “Yes” was considered to denote the presence of LBP. A blinded assessor will evaluate the eligibility criteria. Participants who meet the inclusion criteria will be invited to the main study.

Before the baseline assessment, written consent will be obtained from the participants. At the baseline assessment session, participants will be requested to complete the VAS, Revised ODI, and Borg-10 scale. The baseline assessment will be conducted before the random distribution of the participants into the groups. After completion of the baseline assessment, participants will be randomly assigned into one of the two groups (AB-group or C-group), and simultaneous implementation of the two programs will commence. To improve adherence, participants from AB-group will send daily reports about hours in sitting positions and the number of active breaks via the Messenger^®^ application. Participants from C-group will be asked not to look for other treatments outside the trial during the interventions.

The assessment of the outcomes will be collected at baseline and immediately after the 12-week intervention.

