### 2.11. Study Procedures

#### 2.11.1. Sample Size

The sample size was determined using the software G*Power 3.1, which used Factorial ANOVA with assumption of a medium-sized effect (d = 0.50) at a significance level of 0.05 and statistical power of 0.85. Therefore, the required sample size for this study will be 50 participants randomly assigned in two different groups. The sample will be increased by 20% to compensate for possible dropouts, leading to 32 individuals in each group (overall sample = 64 participants).

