#### 2.11.2. Randomization

Randomization will be performed by a researcher not involved with recruiting and assessing the participants and will be generated via Microsoft Excel software 2019, before the beginning of the main study. Randomization will be stratified according to gender and the frequency of LBP. Treatment allocation will be concealed through sealed, opaque envelopes sequentially numbered. After the baseline assessment, one of the researchers responsible for the intervention will open the sealed envelopes to identify the group to which the participant was allocated: (1) with active breaks (AB-group); (2) with self-care recommendations (C-group).

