### 3.1. Statistical Analysis

The data will be analyzed using Statistica 14.0.0.15 program (TIBCO Software Inc., Palo Alto, CA, USA, 2020). The parameters will be described using basic descriptive statistical measurements, i.e., the percentage for qualitative variables, and the mean and standard deviation for quantitative variables. For variables that do not meet the criteria of normality of distribution, data will be presented as medians and quartile ranges. The normality of the distributions of the quantitative variables under study will be tested using the Shapiro–Wilk test. To verify the homogeneity of variances, Lavene’s test will be conducted. The chi-square test will be used for categorical variables. Descriptive statistics will be calculated separately for all groups (active break vs. control). The Student’s *t*-test (if data meet the criteria of normality of distribution) and the Mann–Whitney U test (if data do not meet the criteria of normality of distribution) will be used to compare parameter values between groups (active break vs. control). The Wilcoxon signed rank test will be used to examine the differences in parameters (VAS, ODI and discomfort) before and after the intervention. Intention-to-treat analysis will include all randomized patients. The significance level will be set at *p* < 0.05.

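### The arms are compared by a valid but unadjusted test that leaves baseline scores and stratification factors unused, and nothing says that this test, not the before–after test, decides effectiveness

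*Protocol article*

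**What the plan says.** All of the following is in the protocol article.

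- **Between arms (section 3.1).** A Student's t-test, or a Mann–Whitney U test where normality fails, "will be used to compare parameter values between groups (active break vs. control"). The text does not say whether the values are week-12 scores or changes from baseline.
- **Before versus after (section 3.1).** "The Wilcoxon signed rank test will be used to examine the differences in parameters (VAS, ODI and discomfort) before and after the intervention". It does not say whether this is run per arm or on both arms pooled.
- **Categorical variables (section 3.1).** "The chi-square test will be used for categorical variables". No stratification is mentioned.
- **Level (section 3.1).** "The significance level will be set at *p* < 0.05". No test is named as the one that decides effectiveness.
- **Baseline data (section 2.10).** "At the baseline assessment session, participants will be requested to complete the VAS, Revised ODI, and Borg-10 scale". On timing: "The assessment of the outcomes will be collected at baseline and immediately after the 12-week intervention".
- **Allocation (section 2.11.2).** "Randomization will be stratified according to gender and the frequency of LBP".
- **Sample size (section 2.11.1).** The calculation is one "which used Factorial ANOVA with assumption of a medium-sized effect (d = 0.50"), with significance level 0.05 and power 0.85. It gives 50 participants, raised to 32 per arm for 20% dropout. Section 3.1 names no factorial ANOVA.

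**The concern.** Two things are at stake.

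**Precision.** A baseline score usually predicts the later score on the same scale. Comparing week-12 scores without it leaves explainable variance in the error term. Stratifying the allocation on sex and pain frequency and then leaving both out of the analysis also forgoes precision if they predict outcome. In a trial of 64 this matters, and adjustment needs no new data.

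**Interpretation.** A signed rank test is paired. Run per arm or pooled, it cannot compare active breaks with control. Participants enter because they report recent low back pain, so improvement in both arms without any treatment effect is plausible. The three scores are named only in the before–after sentence, and nothing states that the conclusion rests on the between-arm contrast. A report could therefore be written around significance in one arm and not in the other.

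**Working it through.** **The plan's own figure.** The 50 does not follow from the stated inputs. A two-group test at d = 0.50, two-sided 0.05 and power 0.85 needs 73 per arm (146 in total). A factorial ANOVA with f = 0.25 (d = 0.50 for two groups) and 1 numerator df also needs 146. The dropout step does reproduce: 25/0.8 = 31.25, so 32 per arm and 64 in total. The sample size is a separate point; here it only supplies the numbers per arm.

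**Inputs.** d = 0.50 and 25 evaluable or 32 randomised per arm (section 2.11.1); significance level 0.05 (section 3.1), taken as two-sided. Section 3.2 drops missing cases, so the number analysed should lie between 25 and 32 per arm. The baseline–outcome correlation r is not in the documents; 0.3, 0.5 and 0.7 are assumed.

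**Power.** All from the noncentral t distribution.

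- Week-12 scores, unadjusted: noncentrality d·√(n/2), df 2n − 2. At n = 25: 0.5 × √12.5 = 1.768, power 0.41. At n = 32: 0.5 × √16 = 2.000, power 0.50.
- ANCOVA on baseline: residual variance falls by the factor 1 − r², that is 0.91, 0.75 and 0.51. Noncentrality is d·√(n/2)/√(1 − r²), df 2n − 3. At n = 32 and r = 0.5: 2.000/0.866 = 2.309, power 0.62.
- Change scores, unadjusted: the SD of change is √(2(1 − r)) in units of the outcome SD. At n = 32 and r = 0.5 this is 1, so power equals the week-12 comparison, 0.50.

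| Analysis | n per arm | r = 0.3 | r = 0.5 | r = 0.7 |
|---|---|---|---|---|
| Week-12 scores, unadjusted | 25 | 0.41 | 0.41 | 0.41 |
| Change scores, unadjusted | 25 | 0.31 | 0.41 | 0.61 |
| ANCOVA | 25 | 0.44 | 0.52 | 0.68 |
| Week-12 scores, unadjusted | 32 | 0.50 | 0.50 | 0.50 |
| Change scores, unadjusted | 32 | 0.38 | 0.50 | 0.72 |
| ANCOVA | 32 | 0.54 | 0.62 | 0.79 |

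By the normal approximation, 85% power needs 72 per arm unadjusted, and 66, 54 or 37 with ANCOVA at r = 0.3, 0.5 or 0.7. These figures credit no gain from the strata and charge no degrees of freedom for them. How strongly sex and pain frequency predict outcome is not given, so that gain cannot be computed.

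**Before–after tests read as evidence.** Suppose both arms improve equally, by dz SDs of change, and each is tested separately. If p is the power of one paired test, active break is significant and control is not with probability p(1 − p), which cannot exceed 0.25. With a paired t-test standing in for the signed rank test at n = 32:

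| dz | p | p(1 − p) |
|---|---|---|
| 0.2 | 0.194 | 16% |
| 0.3 | 0.376 | 23% |
| 0.4 | 0.592 | 24% |
| 0.5 | 0.782 | 17% |
| 0.6 | 0.908 | 8% |
| 0.8 | 0.992 | under 1% |

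At n = 25 and dz = 0.4, p = 0.484 and p(1 − p) = 25%.

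A simulation of the signed rank test itself used 4,000 trials per setting, equal improvement of 0.3 or 0.5 outcome SD, and the same three correlations. The active-break-only pattern appeared in 13–25% of trials at 25 per arm and 6–24% at 32 per arm. In the same trials the between-arm t-test rejected in 4–5%.

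**The case against.** The strongest reply is that a valid between-arm test is already planned. That stands: its error rate is about 5% when the arms do not differ, and leaving out prognostic strata makes it conservative, not liberal.

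Four stronger readings are tempting, and the documents do not support them.

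- **The plan will produce a false claim of effect.** Section 3.1 nowhere says that effectiveness is judged on the before–after tests, or that they are run per arm. The risk arises only if they are read that way, which the text leaves open.
- **Baseline is ignored.** The between-arm sentence does not exclude change scores, and these use baseline, though less efficiently than ANCOVA at every correlation examined. What is supported is an unspecified endpoint and no adjustment.
- **About a quarter of null trials would mislead.** That is the top of the range. The figure depends on the assumed improvement and falls below 1% when improvement is large.
- **Choosing the test by a normality check is itself an error.** No inflation of error has been shown here, and a rank test is reasonable for bounded scores.

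Two further objections hold in part. The power gain rests on an assumed correlation and is small at 0.3. And a condensed article may leave covariates to a fuller plan; the factorial ANOVA in the sample-size section hints that a model could exist. But section 3.1 does more than stay silent: it names the tests, and the named tests are unadjusted.

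**Conclusion.** Should-fix: a free improvement in efficiency and a needed clarification, not an invalid analysis.

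For d = 0.50 and r from 0.3 to 0.7, baseline adjustment adds 3 to 27 percentage points of power at 25 per arm (0.41 to 0.44–0.68) and 4 to 29 at 32 per arm (0.50 to 0.54–0.79). A reader might infer that adjustment rescues the sample size. It does not: 0.85 is not reached at any of these correlations.

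The interpretive risk is conditional. It is under 1% to 25% per outcome for equal improvements of 0.2 to 0.8 SD of change, and applies only if separate per-arm tests are taken as evidence. Three outcomes would be exposed to it.

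**What to change.** Amend section 3.1 as follows.

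1. **VAS, ODI and Borg:** make the main analysis an ANCOVA of the week-12 score on arm, baseline score, sex and baseline pain frequency. Report the adjusted between-arm difference with its 95% CI, and give a rank-based analysis as sensitivity. This also settles whether final or change scores are compared.
2. **Global Perceived Effect and pain frequency:** ANCOVA does not fit the dichotomised Global Perceived Effect, which has no baseline, or a categorical frequency. Compare the arms by categorical methods that account for the strata, and for pain frequency also for its baseline level.
3. **Before–after Wilcoxon tests:** say whether they are per arm or pooled, label them descriptive, and state that effectiveness is judged on the between-arm difference alone.
4. If a fuller plan already holds an adjusted model, bring section 3.1 into line with it.

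The cost is wording only. Baseline scores, sex and pain frequency are already collected.

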### 3.2. Missing Data

Lack of data may occur as a result of discontinuation of participation in the program or as a result of unexpected random events (e.g., illness). Since missing cases are expected to be less than 10% of the initial number of patients, the data will be analyzed as a full case study, excluding missing data from the analysis.

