### 2.8. Active Break Program

The experimental group will receive recommendations to take an active break every 30 min of sitting for 12 weeks. In the experimental intervention, the active break program will include lumbar and hip extension exercises and will be based on self-education with an explanation of the importance of regular training. The participants will receive a booklet with photographed and described exercises. The education will be carried out by an experienced physiotherapist.

The habit of doing exercises during an active break will be formed gradually (Table 2). In the first month, participants will be instructed to perform the proposed exercises in a standing position with lumbar and hip extension every 30 mins or whenever musculoskeletal discomfort occurs. In the second month, the complexity of the active break exercises will be increased by progressing to spine hyperextension exercise. In the third month, participants will be instructed to also perform spine hyperextension exercise in a sitting position. The number of repetitions depends on the needs of the participants.

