### 2.9. Control Group

Participants assigned to the control group will receive an educational self-care book containing information on LBP, the anatomy of the spine and its relationship to the muscular chain, care during daily life activities and the importance of regular physical exercises. The control group will perform their regular baseline activities and will be advised to not alter their current behavior routine. Participants will be asked not to look for other treatments outside the trial during the intervention period.

Participants assigned to the control group will be offered the option of joining the exercise program with an active break after the final assessment has been completed.

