The strength of the study described here is the simple design and low-cost exercise training intervention. Students will perform exercises that will hardly be noticeable to the environment while sitting, what we called an active break. The active break program will be based on work- and home-based exercises. Self-management has an added value in the treatment of people with non-specific LBP. Work- or home-based exercises will save time and money, and are very convenient and hassle-free for participants. Facilitating people’s independence with LBP and providing tools that allow them to self-manage are generally considered important. Our main research outcome will be developed to match the needs of young people with LBP and the possibilities of the environment, to reduce LBP and musculoskeletal discomfort during prolonged sitting, and consequently, maintain health and quality of life. The intervention will address the social and health needs of a particular social group: young people, with the possibility of extending the recommendations to other groups. The research outcomes will build evidence-based practices for students, teachers, health professionals, personal trainers and family doctors.

We may face the major limitation of dropout of participants taking into account the length of the intervention (12 weeks). Therefore, to avoid a high dropout rate, we planned a system of rewards during the intervention and a gift for all students at the end of the final assessment. We cannot also exclude the occurrence of bias regarding monitoring the frequency and quality of sitting breaks each day. Other limitations that will arise during data collection and analysis will be identified and explained at the data presentation stage.

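### Section 3.2 counts stopping the programme as a source of missing data and drops those cases, which risks unequal, outcome-related loss at week 12 despite the intention-to-treat promise

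*Protocol article*

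**What the plan says.** Section 3.2 (Missing Data) gives two causes of missing data, and the first is leaving the programme: "Lack of data may occur as a result of discontinuation of participation in the program or as a result of unexpected random events (e.g., illness". It then sets the handling. "Since missing cases are expected to be less than 10% of the initial number of patients", it says, "the data will be analyzed as a full case study, excluding missing data from the analysis".

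Section 3.1 (Statistical Analysis) states: "Intention-to-treat analysis will include all randomized patients".

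The arms differ in what there is to stop. Section 2.8: "The experimental group will receive recommendations to take an active break every 30 min of sitting for 12 weeks". The exercises progress monthly, and section 2.10 adds daily reports through a messaging application for this arm only. Section 2.9: "The control group will perform their regular baseline activities and will be advised to not alter their current behavior routine". Controls receive a book and are offered the exercise programme once the final assessment is done.

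The Discussion expects attrition: "We may face the major limitation of dropout of participants taking into account the length of the intervention (12 weeks". It plans rewards during the intervention and a gift for all students at the end of the final assessment.

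Sections 2.2 and 2.10 place outcome collection at baseline and immediately after the 12 weeks. Section 3 has the coordinator text participants every second day.

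**The concern.** Stopping an intervention and leaving a trial are different events. A student who gives up the breaks can still complete a pain scale, the ODI and the GPE at week 12, and an intention-to-treat comparison needs those values. Section 3.2 names the first event as a cause of lost data and removes the cases. The article never says that such a student is still invited to the final assessment. Staff deciding whom to call back have only this wording to go on.

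The consequence need not be equal between arms. A participant asked to break every 30 minutes, to progress through the exercises and to report daily has several reasons to stop. A control has almost nothing to stop and some reason to attend the last visit. If those who stop active breaks tend to be those who were not helped, leaving them out makes the intervention look better than it is. With one assessment after baseline, there is no interim value to stand in for a lost result.

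**Working it through.** **1. The plan's own figures on loss.** Section 2.11.1 starts from 50 participants (25 per group) and allows 20% dropout: 25 / (1 − 0.20) = 31.25, rounded up to 32 per group and 64 overall. This reproduces the stated figures. Section 3.2 expects under 10% missing: 0.10 × 64 = 6.4, so at most 6 people. Neither figure is split by arm.

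**2. What an overall ceiling permits in one arm.** Six of 64 is 9.4%, inside the ceiling. If all six are in the active break arm, 6 / 32 = 18.8% of that arm is lost against 0% of controls. A small overall percentage therefore does not secure balance.

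**3. Bias formula.** Let q be the share of an arm that is lost. Let g be how much worse, in SD, the lost are at week 12 than the retained. The full-arm mean is worse than the retained mean by q × g. A complete-case comparison is then biased in favour of active breaks by

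bias = q(active) × g(active) − q(control) × g(control).

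**4. Numbers.** The documents give no value for g. I assume 0.5 to 1.0 SD, with no loss among controls.

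| Lost from active arm | q | g = 0.5 | g = 1.0 |
|---|---|---|---|
| 3 of 32 | 0.094 | 0.05 SD | 0.09 SD |
| 6 of 32 | 0.188 | 0.09 SD | 0.19 SD |

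Against the planned d = 0.50, the second row is 0.094 / 0.50 = 19% to 0.188 / 0.50 = 38%.

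**5. Direction.** If 3 are lost from each arm with the same g, the two terms cancel and the bias is 0. If those who stop active breaks do so because they have improved, g(active) is negative and the bias turns against active breaks. The same happens if mainly disappointed controls with poor outcomes leave.

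**6. Effect on the test.** In a simulation with no true effect (32 v 32, six removed from the active arm, two-sided t-test, 20,000 runs), the rejection rate was 0.048 when loss was unrelated to outcome. It was about 0.07 when the lost averaged 0.57 SD worse (bias 0.11 SD) and about 0.13 when they averaged 1.13 SD worse (bias 0.21 SD).

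**7. After the change.** If those who stop are still assessed, loss from this cause is zero and q × g vanishes, whatever g is.

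**The case against.** The best reply is that section 3.2 describes what may happen and sets no rule. No section withdraws a non-adherent participant. Sections 2.2 and 2.10 attach no adherence condition to the final assessment, and section 3 treats logs and texts purely as adherence. The word for programme could also mean the study, because section 2.10 speaks of two programmes, one per arm. On that reading 3.2 refers to ordinary dropout in either group. What remains would be an unstated follow-up detail, which an article may leave to a fuller document.

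Much of this stands. A reader might infer that the plan withdraws anyone who stops, or that outcomes will be lost selectively from one arm. The documents support neither. They also contain mitigation: the gift at the final assessment, and in Table 2 a milder variant for participants sensitive to hyperextension.

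The point nevertheless rests on stated text and not on silence alone. Section 3.2 names stopping as a cause and excludes the cases, while 3.1 promises all randomised patients. Those two statements are compatible only if people who stop are still measured. Sections 2.6 and 2.9 use the word for the active break programme, and an ambiguity over whom to assess is itself worth removing.

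Two further limits are accepted. Baseline VAS, ODI and Borg scores are available, so baseline-adjusted or sensitivity analyses could reduce or bound the bias, although they cannot replace unobserved outcomes. And the Borg measure needs one hour of sitting, with tests done in the laboratory, so it cannot be collected remotely.

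**Conclusion.** The point holds as a foreseeable risk created by the wording of 3.2 and by its conflict with 3.1. Under the section's own ceiling, with all loss in the active break arm and those lost 0.5 to 1.0 SD worse, the bias is about 0.09 to 0.19 SD in favour of active breaks. With three lost it is 0.05 to 0.09 SD. These figures rest on an assumed gap and an assumed one-sided loss, and the true bias could be smaller, nil or reversed.

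A larger figure is tempting. If exactly the worst 20% of the active arm left and no control did, the bias would be 0.280 / 0.8 = 0.35 SD, or 70% of d = 0.50. That is an extreme bound. The 20% allowance covers both groups, and nothing in the article suggests that loss would follow outcome so exactly. It should not be read as the expected size.

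The change should be made because it is cheap and acts on conduct, while outcomes can still be collected.

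**What to change.** In sections 3 and 3.2:

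- State that stopping the breaks, the logs or the daily reports is non-adherence and not withdrawal from the study.
- Invite every randomised participant in both arms to the week-12 assessment, regardless of adherence.
- Where the visit is missed, seek ODI, GPE and a pain rating remotely, by the same means in both arms, and flag the values as remote. The Borg sitting test stays missing.
- Count as missing only those who withdraw consent to assessment or cannot be reached.
- Report missingness and the reasons for it by arm.
- Reconcile the all-randomised statement in 3.1 with the exclusion in 3.2.

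Nothing here alters the exercises or who may stop them. The cost is protocol wording and a few reminder messages, to students of one faculty whom the coordinator already texts. The downsides are small: some outcomes come by a different mode (the VAS is a measured mark on a 10 cm line), and the estimate, now including those who stopped, may be slightly less favourable.

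### The plan promises an intention-to-treat analysis of everyone randomised, but its missing-data rule keeps complete cases only and states no fallback if loss exceeds the expected 10%

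*Protocol article*

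**What the plan says.** The protocol article addresses the analysis set and missing data in four places.

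- Section 3.1 (Statistical Analysis): "Intention-to-treat analysis will include all randomized patients".
- Section 3.2 (Missing Data) gives a cause, "Lack of data may occur as a result of discontinuation of participation in the program", alongside chance events such as illness. It then gives an expectation, "Since missing cases are expected to be less than 10% of the initial number of patients", and draws a rule from it: "the data will be analyzed as a full case study, excluding missing data from the analysis".
- Section 2.11.1 (Sample Size): "the required sample size for this study will be 50 participants randomly assigned in two different groups". It continues: "The sample will be increased by 20% to compensate for possible dropouts". The stated result is 32 per group, 64 overall.
- Section 4 (Discussion): "We may face the major limitation of dropout of participants taking into account the length of the intervention (12 weeks". The following sentence plans rewards and a closing gift to keep dropout low.

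Outcomes are collected at baseline and once more, directly after the 12-week intervention (sections 2.2 and 2.10, Table 1). The Global Perceived Effect (GPE) is collected only at the end (section 2.4).

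**The concern.** The term used in section 3.2 for the analysis is unusual, but the words after it leave no doubt that participants with missing data are left out. That is a complete-case analysis, and it does not include everyone randomised. The two rules govern the analysis set for every primary outcome, so the trial cannot follow both.

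Two things are at stake. First, a complete-case result would be published under an intention-to-treat label; and while both rules stand, the choice between them could be made after the data are seen. Second, the comparison of completers is biased if loss is related to outcome and that relation differs between arms. The article gives grounds to take this seriously. It names leaving the programme as a cause of missing data. Only the AB arm is asked to exercise at every half hour of sitting and to send daily reports (sections 2.8 and 2.10). If AB participants who do badly are the ones who leave, the remaining AB arm looks better than the arm that was randomised.

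**Working it through.** **1. Can both rules hold?** Take one randomised participant with no week-12 visit.

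- Under section 3.1 this participant belongs in the analysis.
- The only other scores are from baseline. The t-test or Mann–Whitney comparison at week 12 has no value to use, the Wilcoxon before-after test has no pair, and GPE has no value at all.
- Under section 3.2 the participant is excluded, and the article states no method that would bring the participant back in.

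So the rules agree only if no week-12 value is missing.

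**2. Reproducing the planned sample size.** Inputs from section 2.11.1: 50 required in two groups, taken as 25 per group; 20% for dropouts.

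- Dividing by the retained share: 25 / (1 − 0.20) = 31.25, rounded up to 32 per group; 2 × 32 = 64. This matches the stated total.
- A literal 20% increase would give 50 × 1.20 = 60, which does not match.

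The 64 therefore corresponds to a planned loss of 20% of those randomised.

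**3. What the two loss figures mean out of 64.**

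- Section 3.2, under 10%: 0.10 × 64 = 6.4, so at most 6 excluded and at least 58 analysed.
- Section 2.11.1, 20%: 0.20 × 64 = 12.8, so about 13 excluded and about 51 analysed.
- For comparison, an allowance of 10% would give 25 / 0.90 = 27.8, so 28 per group and 56 in total.

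The sample size makes room for about twice the loss on which the complete-case rule rests.

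**4. Illustration of the bias.** Let p be the share of the AB arm lost, C the mean of AB completers and D the mean that AB dropouts would have had. The mean of the full AB arm is (1 − p)C + pD, so the completers' mean differs from it by C − [(1 − p)C + pD] = p(C − D). If control loss is unrelated to outcome, this is the bias in the group difference.

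The article gives no value for the gap between dropouts and completers. A range of 0.5 to 1.0 SD is assumed here.

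| AB loss | gap 0.5 SD | gap 1.0 SD | share of the planned d = 0.50 |
|---|---|---|---|
| 10% | 0.10 × 0.5 = 0.05 SD | 0.10 × 1.0 = 0.10 SD | 10% to 20% |
| 20% | 0.20 × 0.5 = 0.10 SD | 0.20 × 1.0 = 0.20 SD | 20% to 40% |

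**The case against.** **The two loss figures need not conflict.** A reader might infer that 20% in section 2.11.1 contradicts under 10% in section 3.2. The article does not support that. The first is an allowance for possible loss, the second an expectation, and a safety margin may exceed what is expected. They are different planning assumptions, not an arithmetic error. The Discussion says only that dropout may become a major limitation, and it plans incentives against it. Section 3 adds text contact every second day, meetings and feedback, so a loss under 10% is not implausible. What remains is that the optimistic figure is the sole reason for the rule, and nothing is stated for the case where it fails.

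**Complete-case analysis does not strictly need data missing completely at random.** That stronger reading is tempting but wrong. Loss that depends on arm alone does not bias the difference in means. Nor does loss that depends on baseline score in the same way in both arms, if the treatment effect is additive. The concern is limited to outcome-related loss that differs by arm.

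**The direction of bias is not established.** The exercises can be adapted: repetitions follow the participant's needs (section 2.8), and those sensitive to hyperextension use an extension version (Table 2). Controls may also leave for reasons tied to their pain, which could offset or reverse the bias. Someone who stops exercising but attends at week 12 is still analysed. These points stand, so the figures above illustrate size and do not predict it.

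**Some detail belongs in a statistical analysis plan.** True, and the absence of an imputation model or sensitivity analysis from the article is not the point here. The point is that two statements in the article exclude each other, and further detail elsewhere would not remove that.

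**Conclusion.** The point holds as a conflict between sections 3.1 and 3.2. With a single week-12 assessment, the first missing visit makes the promised intention-to-treat analysis impossible under the stated missing-data rule. This conclusion needs no assumption about how much is lost or why, and it is reason enough to change the text.

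The loss figures add a second, lesser weakness: the rule is justified by at most 6 of 64 missing, while the sample size provides for about 13, and the article states no fallback.

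The possible bias is 0.05 to 0.10 SD at 10% AB loss and 0.10 to 0.20 SD at 20%. It rests on an assumed gap of 0.5 to 1.0 SD in the AB arm and on control loss unrelated to outcome. It shows that a loss near 10% does not by itself make the rule safe; it does not show that the trial will be biased by that amount.

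**What to change.** Replace the rule in section 3.2 with a primary analysis of all randomised participants in their assigned arm. Two suitable options are:

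- multiple imputation by arm, using baseline score, gender and LBP frequency; or
- for outcomes measured twice, a longitudinal model with baseline and week-12 scores as outcomes.

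Keep the complete-case analysis as a sensitivity analysis.

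Both options assume data missing at random. With one post-baseline visit, dropouts contribute baseline information only, so neither method removes bias from outcome-driven dropout. Therefore add a delta-adjusted sensitivity analysis that shifts the imputed scores step by step, and report how far they must move before the conclusion changes. Also seek week-12 outcomes from participants who stop the exercises. This has to be arranged before follow-up ends, because no analysis recovers values that were never collected.

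If the sponsor prefers to keep the complete-case rule, section 3.1 should drop the claim to include everyone randomised, and the analysis should be labelled complete case.

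The cost is a change of wording, a little more analysis work and some follow-up effort. The sample size does not change on account of this point.
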